### Surgical technique

The surgical procedures (plate fixation or hemiarthroplasty) are performed by shoulder-oriented orthopedic surgeons of the Tampere, Kuopio, Turku, and Oulu University hospitals. In this trial, we will use the Philos locking plate system (Synthes®, Solothurn, Switzerland) and an uncemented Epoca fracture prosthesis (Synthes®, Solothurn, Switzerland) with a hydroxyapatite coating. Additional cement fixation will be used if necessary. All patients randomized to surgical treatment will undergo the surgery within 2 weeks after the fracture. During the operation, the Neer’s classification and evidence of potential rotator cuff rupture will be recorded.

Patients will be placed in the beach-chair position. Plexus anesthesia will be used when possible. The deltopectoral, deltoid-split, or minimally invasive plate osteosynthesis approach will be used. Cuff tendons will be routinely inspected and sutures passed through each tendon to ease the handling of the fragments. For plating, the fragments will be preliminarily reduced with sutures and k-wires. The plate will be placed lateral from the biceps groove and 5 mm distal from the tip of the tuberculum majus. Six to eight locking screws will be placed in the head and three conventional or locking screws will be placed in the shaft.

The prosthesis height will be determined from the medial rim of the articular fragment. Anatomic retroversion will be determined from the shaft configuration. Reaming will be performed until the trial stem is stable. If needed, a minimal amount of cement will be used to stabilize the stem. Head size is determined from the articular fragment. The offset will be left to neutral. Before tightening the cables underneath the tuberculi, bone grafts from the head fragment will be placed against the stem. Sutures will be knotted to secure the cuff.

Drainage will be left in if necessary and the wound closed in layers. The shoulder will be immobilized with a collar-cuff in the operating theater.

### Conservative treatment

Patients randomized to non-operative treatment will be instructed with regard to joint mobilization by a physiotherapist during hospitalization. Patients will receive a written aftercare protocol with detailed pictures. A collar-cuff or a sling will be used for 3 weeks to relieve pain. During the first 3 weeks, pendulum exercises are allowed, and free joint mobilization and normal limb activation throughout treatment will be strongly supported. Active ROM exercises, as allowed by pain, will begin at 3 weeks. Physiotherapist contacts will be arranged to begin 3 and 6 weeks after surgery and all patients will have 5 physiotherapist contacts within the 3 first months.

### Postoperative aftercare

Patients operated with a plate will follow the same protocol as in conservative treatment. Patients treated with a prosthesis will wear a sling for 6 weeks. Two weeks postoperatively, they will begin pendulum movements. Free, active mobilization will be allowed at 6 weeks. Patients will be advised to mobilize their free joints from the beginning of the treatment and normal limb activation during aftercare will be supported. Contact with a hospital physiotherapist will begin after 3 and 6 weeks postoperatively and all patients will have 5 physiotherapist contacts within 3 months from the beginning of treatment. Patients will receive a detailed written aftercare protocol with instructional pictures and formal physiotherapy will be instructed before leaving the hospital.

### Follow-up

Follow-up will be carried out at the orthopedic outpatient clinic of the hospital where the patient was primarily treated. The patients will visit the outpatient clinic at 6 weeks and 3 months. Ultrasound examination of the fractured shoulder to assess possible rotator cuff injury will be performed at the 3-month visit by an experienced musculoskeletal radiologist.

Orthopedic outpatient clinic visits will be continued if necessary. In addition to these visits, in each center a blinded physiotherapist or sports physiologist will perform a research examination at 6 months, and 1, 2, 5, and 10 years from the beginning of the treatment. Patients are supposed to wear a shirt to blind the examiner. During these visits, radiographs will be taken of the treated shoulder, ROM and Constant-Murley scores of both shoulders will be obtained, and the patient will complete the EQ-5D, 15D, DASH, and OSS questionnaires.

Should any adverse event demanding separate outpatient or inpatient care or surgery occur during the follow-up, an adverse event form will be completed within 24 hours of the execution of treatment. The information will be sent to the research coordinator. If the patient is not willing to continue in the study, or does not appear at appointments, or dies, a research discontinuation form will be completed. The study flow is outlined in Figure 1 and assessments and procedures are outlined in Table 1.

**Figure 1 F1:**
[figure not shown]
**Study flow. **Stratum I for 2 part fractures, Stratum II for 3 and 4 part fractures.

**Table 1 T1:** Assessments and procedures of the trial

**Assessment**	**Preoperative**	**1. visit 6 weeks**	**2. visit 3 months**	**3. visit 6 months**	**4. visit 1 year**	**5.visit 2 years**
x-ray	X	X	X	X	X	X
CT	X					
Ultrasound			X			
Ex-/inclusion	X					
Medical history	X					
Consent	X					
Questionnaire	X		X	X	X	X
VAS-pain	X			X	X	X
EQ-5D	X			X	X	X
15D	X			X	X	X
OSS	X			X	X	X
DASH	X			X	X	X
Constant-Murley Score				X	X	X
Doctors visit		X	X			
Research visit				X	X	X

### Power analysis

In Stratum I, when assuming an effect size of a 10-point difference in the DASH score and a standard deviation of 15 points, the estimated sample size is 37 patients (delta = 10, sd = 15, alpha = 0.05, power = 0.8). Thus Stratum I requires 74 patients (2 comparison groups). In Stratum II, when assuming an effect size of a 10-point difference in the DASH score and a standard deviation of 15 points, the estimated sample size is 66 patients (ANOVA, alpha = 0.05, power = 0.8). The number of comparison groups is three. The total number of patients in Stratum II is 198. Thus, the total number of patients in the study will be 272. We will assume a 10% drop-out rate in both groups; therefore, the total patient number required will be 299 (81 + 218). In cases in which the patient changes to a different treatment group, they will be analyzed according to the intention-to-treat principle. SD value has been estimated after Gummerson *et al.* (2003). The article describes the minimal detectable change in DASH as 10 points with an SD of 13 with a mean score of 15 points [28].

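### The Stratum II figure of 66 patients per arm does not follow from its stated inputs: they need at most 45 per arm, and 66 gives about 94% power, not 80%

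*Protocol article*

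**What the plan says.** All the relevant text is in the Protocol article, section Power analysis.

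- Effect and spread: "In Stratum II, when assuming an effect size of a 10-point difference in the DASH score and a standard deviation of 15 points".
- Test, error rates and result: "the estimated sample size is 66 patients (ANOVA, alpha = 0.05, power = 0.8").
- Arms: "The number of comparison groups is three".
- Total: "The total number of patients in Stratum II is 198". Since 3 × 66 = 198, the 66 is per arm with equal allocation.
- Drop-out, added afterwards: "We will assume a 10% drop-out rate in both groups; therefore, the total patient number required will be 299 (81 + 218"). Since 198 × 1.1 = 217.8, the 66 is a figure before drop-out.
- Stratum I, with the same difference and SD: "the estimated sample size is 37 patients (delta = 10, sd = 15, alpha = 0.05, power = 0.8").
- Source of the SD: "The article describes the minimal detectable change in DASH as 10 points with an SD of 13 with a mean score of 15 points".

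The section states no pattern for the three means, no multiplicity allowance, and no inflation other than drop-out.

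**The concern.** Both strata use the same 10-point difference and SD of 15. Stratum I needs 37 per arm and Stratum II is given 66. A third arm and an omnibus F test raise the requirement, but not by that much. If 66 does not come from the stated inputs, the stated 80% power is not the power of the design. Stratum II is 198 of the 272 patients before drop-out (73%), so the mismatch affects most of the trial. A reader cannot tell whether the number is a miscalculation or reflects an assumption that was left out.

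**Working it through.** **Inputs** (all from Power analysis): k = 3 arms, largest DASH difference 10, SD 15, alpha 0.05, power 0.80, equal n per arm. The pattern of means is not stated, so I bracket it.

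**1. Check on Stratum I.** Two-sided t-test, difference 10, SD 15, alpha 0.05: 37 per arm is the smallest n with at least 80% power. The protocol's 37 reproduces, so its conventions are read correctly.

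**2. Formula for Stratum II.** One-way ANOVA, noncentral F with 2 and 3(n − 1) degrees of freedom and noncentrality λ = n × S / SD², where S is the sum of squared deviations of the three means from their average.

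**3. Least favourable pattern.** With the outer means at 0 and 10 and the third at x, S = 50 + (2/3)(x − 5)². The minimum is 50, at x = 5. The maximum is 66.7, at x = 0 or 10. The midpoint pattern therefore gives the largest n that a 10-point range can require.

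**4. Means 0, 5, 10.** Cohen's f = √(50/3)/15 = 4.08/15 = 0.272, and λ = n × 50/225.

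| n per arm | λ | Power |
|---|---|---|
| 44 | 9.78 | 79.6% |
| 45 | 10.00 | 80.6% |
| 66 | 14.67 | 93.6% |

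The requirement is 45 per arm, or 3 × 45 = 135. With the protocol's drop-out method, 135 × 1.1 = 148.5, rounded up to 149.

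**5. Means 0, 0, 10.** f = √(66.7/3)/15 = 0.314. The requirement is 34 per arm, and 66 per arm has 98.2% power.

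**6. What would make 66 right at 80% power** (evenly spaced means, alpha 0.05): an SD of about 18.4 with a 10-point range, or a range of about 8.2 points with SD 15. Neither is stated.

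**7. Other readings of the paragraph.**

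| Reading | n per arm |
|---|---|
| SD 13 (the cited source), means 0, 5, 10 | 34 |
| 10 points between neighbouring means (0, 10, 20) | 12 |
| Tukey pairwise | 48 or fewer |
| Bonferroni pairwise t-test, alpha 0.05/3 | 49 |
| Scheffé pairwise | about 50 |
| Mann–Whitney inflation of 45 (÷ 0.864) | about 52 |
| Mann–Whitney inflation of the Bonferroni 49 (÷ 0.864) | about 57 |
| ANOVA at alpha 0.05/3 | 58 |
| ANOVA at 90% power | 58 |
| ANOVA at 95% power | 71 |
| ANOVA at alpha 0.01 | 65 |

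Only the last comes close to 66, and it contradicts the stated alpha of 0.05.

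**8. What 66 per arm gives pairwise.** A 10-point contrast by t-test, SD 15, has 96.7% power at alpha 0.05 and 91.8% at Bonferroni alpha 0.0167. At 45 per arm the Bonferroni figure is about 76%.

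**The case against.** **The error is on the safe side.** On the stated inputs Stratum II exceeds its power target under every pattern with a 10-point range, and pairwise contrasts are well powered even after Bonferroni adjustment. Type I error and the planned analysis are untouched. This stands, and it limits the weight of the point. It does not make the stated 80% correct.

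**The pattern of means is unstated, so 45 is not the only answer.** True, but 45 is the ceiling for a 10-point range. The other patterns need fewer, so the gap cannot explain 66.

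**The larger number may be deliberate.** The Statistical analysis section names two-group tests (t-test or Mann–Whitney), and the SD of 15 rests on a single source. A margin for either would be reasonable. The paragraph claims no such margin, and the pairwise and rank-test variants above still fall short of 66.

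Stronger readings are tempting, but the documents do not support them:

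- *That patients are needlessly randomised and the target should fall to 45 per arm.* The excess is 198 − 135 = 63 before drop-out, or 218 − 149 = 69 randomised, but only relative to the stated inputs. At an SD of about 18.4 there is no excess, and at 45 per arm Bonferroni contrasts would have only about 76% power. Cutting enrolment is a design choice, not a correction of this paragraph.
- *That the cause is known.* Entering the variance of the means with divisor 3 (50/3 = 16.7) where a routine expects divisor 2 (50/2 = 25) gives 79.97% power at n = 66. The protocol mentions no such routine, and strict rounding up would give 67. This is conjecture.
- *That a null result would be misjudged.* Nothing says that results will be read against the planning difference. The Statistical analysis section promises 95% confidence intervals, which show what is excluded whatever the planned n.

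**Conclusion.** The point holds as an error of statement. With three groups, a 10-point range, SD 15 and alpha 0.05, the ANOVA needs at most 45 per arm (135; 149 with drop-out), not 66 (198; 218). The 66 per arm has 93.6% power for evenly spaced means and 98.2% when one arm stands apart, against the stated 80%. The result assumes that the 10 points is the largest difference between any two arms, with equal arms, normal errors and a common SD. Reading it as the smallest difference only lowers the requirement. The misstatement is conservative, so Stratum II is not underpowered for its overall test and no planned inference is invalidated. The sample size and the power that the protocol reports for its larger stratum do not belong together and should be reconciled.

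**What to change.** Keep 66 per arm and rewrite the Stratum II sentences in Power analysis so that inputs, number and power agree:

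- State the pattern of means (for example, evenly spaced over a 10-point range).
- State what 66 per arm delivers at SD 15 and alpha 0.05: about 93.6% power for the overall test at a 10-point range, or 80% power for a range of about 8.2 points. Equivalently, 80% power for 10 points if the SD is about 18.4.
- State the pairwise power: 91.8% for each 10-point t-test contrast at Bonferroni alpha 0.0167.

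Alternatively, if 66 came from an assumption that was left out (a larger SD, a smaller difference, higher power or a multiplicity allowance), state that assumption and show that it gives 66.

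The cost is a few sentences. The totals of 198 and 218 stay as they are, no patients are added, and no analysis changes.

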### Randomization

All patients will be randomized by a Tampere University Hospital research coordinator who will not attend the study. Patients with a two-part fracture will be randomized to either conservative or plate-fixation groups. Patients with multi-fragmented fractures will be randomized to conservative, plate fixation, or prosthesis groups. Both fracture types will be randomized using a random number matrix in block allocation fashion. The blocks will be age-dependent because, based on the literature, age and functional outcome are associated [27]. The treatment allocations from the matrix will be sealed in an envelope. After the patient's enrollment in the study has been confirmed, the research physician will contact the research coordinator, who will open the envelope and the randomized treatment will be carried out. The research coordinator will monitor the study flow. An independent monitoring committee has not been established.

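### The 10% drop-out allowance multiplies by 1.10 instead of dividing by 0.90, so the recruitment target falls about one patient (Stratum I) and two patients (Stratum II) short of the plan's own required numbers

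*Protocol article*

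**What the plan says.** The protocol article's Power analysis section builds the target in three steps.

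- **Stratum I.** The number per group is given as "the estimated sample size is 37 patients (delta = 10, sd = 15, alpha = 0.05, power = 0.8", and from this "Thus Stratum I requires 74 patients (2 comparison groups".
- **Stratum II.** The number per group is given as "the estimated sample size is 66 patients (ANOVA, alpha = 0.05, power = 0.8". Then "The number of comparison groups is three" and "The total number of patients in Stratum II is 198". Adding the strata, "the total number of patients in the study will be 272".
- **Drop-out.** "We will assume a 10% drop-out rate in both groups; therefore, the total patient number required will be 299 (81 + 218".

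The section gives no formula for the last step. It does give the assumed rate, the numbers to which it is applied, and the result.

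**The concern.** The drop-out sentence presents 299 as what follows from needing 272 evaluable patients and losing 10%. The calculation adds 10% of the evaluable number. Drop-out, however, is taken from the larger recruited number, so adding 10% beforehand does not make good a 10% loss afterwards. If recruitment stops at 81 and 218 and the assumed loss occurs, both strata end below the numbers that the section has just called for.

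At stake is whether the target delivers the planned evaluable numbers. This matters more in Stratum I, which was sized close to 80% power. The Objectives section says the strata are reported separately, so a surplus in Stratum II would not help Stratum I.

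**Working it through.** **Inputs, all from the Power analysis section:** difference 10 DASH points, SD 15, alpha 0.05, power 0.80; required 74 (2 x 37) and 198 (3 x 66), total 272; drop-out 10%. Assumption: the test is two-sided. The article does not say so, but a two-sided t-test reproduces 37 per group.

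**1. Reproducing the plan's figures: N x 1.10, rounded to the nearest whole number**

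| | Required N | N x 1.10 | Plan states |
|---|---|---|---|
| Stratum I | 74 | 81.4 | 81 |
| Stratum II | 198 | 217.8 | 218 |
| Total | 272 | 299.2 | 299 |

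All three match. Division by 0.90 gives 82.2, 220.0 and 302.2, and matches none of them.

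**2. Evaluable patients after a 10% loss: recruited x 0.90**

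- Stratum I: 81 x 0.90 = 72.9, against 74 (short by 1.1).
- Stratum II: 218 x 0.90 = 196.2, against 198 (short by 1.8).
- Total: 299 x 0.90 = 269.1, against 272 (short by 2.9).

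**3. Drop-out that the stated targets do cover: 1 - required/recruited**

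- Stratum I: 1 - 74/81 = 8.6%.
- Stratum II: 1 - 198/218 = 9.2%.

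**4. Targets that would cover 10%: required/0.90, rounded up**

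- By stratum: 74/0.90 = 82.2, so 83; 198/0.90 = 220; sum 303.
- By arm: 37/0.90 = 41.1, so 42 x 2 = 84; 66/0.90 = 73.3, so 74 x 3 = 222; sum 306.
- Increase over 299: 4 patients (1.3%) or 7 patients (2.3%).

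**5. Effect on power**

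Stratum I, two-sided t-test (noncentral t), difference 10, SD 15:

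| Evaluable patients | Power |
|---|---|
| 74 (37 + 37) | 80.8% |
| 73 (36 + 37) | 80.2% |
| 72.9 (36.45 per arm) | 80.2% |
| 72 (36 + 36) | 79.7% |

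Stratum II, one-way ANOVA (noncentral F), SD 15. The article does not state how the three means differ, so two patterns are shown:

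| Assumed means | 66 per arm | 65.4 per arm (196.2/3) |
|---|---|---|
| 0, 5, 10 | 93.6% | 93.3% |
| 0, 0, 10 | 98.2% | 98.1% |

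Under both patterns, 66 per arm exceeds what these inputs need for 80% power (45 or 34 per arm). That is a separate question; here 198 is taken as the plan's stated requirement.

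**The case against.** The strongest case on the other side is that nothing of consequence follows. The gap is one patient in one stratum and two in the other. A drop-out rate is itself a guess, and 8.6% or 9.2% is as plausible as 10%. The section also plans with SD 15 while reporting an SD of 13 from its cited source. With SD 13, 36 per arm would give 89.6% power and 28 per arm would be enough for 80%. All of this stands, and it limits the point to a minor one. It does not make the sentence right: the section names a rate and a required number, and the target does not follow from them.

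A reader might draw two stronger conclusions that the article does not support.

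- **That Stratum I drops below 80% power.** The figure of 79.7% needs 72 evaluable patients. The expected number is 72.9, at which power is about 80.2%, so 37 per arm holds a small margin that absorbs the shortfall.
- **That the multiplication spoils equal arms**, because 81 is odd and 218 is not divisible by three. The correctly inflated stratum totals, 83 and 220, do not split evenly either. Unevenness comes from rounding by stratum instead of by arm. The article states no allocation ratio (equal arms are only implied by 37 x 2 and 66 x 3), and a target that does not divide by the number of arms is not an error.

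**Conclusion.** The point holds as a minor arithmetic error. The allowance was applied as N x 1.10 where N/0.90 was needed. The stated 81 and 218 therefore leave about 73 and 196 evaluable patients, against 74 and 198. At the planning values, this lowers Stratum I power by about 0.6 percentage points, to a level still at the planned 80%. In Stratum II the loss is 0.3 points or less. No design choice or analysis depends on it.

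The shortfall rests only on the section's own numbers and on reading the drop-out rate as a share of those recruited. The power figures rest in addition on a two-sided test, SD 15 and, for Stratum II, the assumed patterns of means.

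**What to change.** Choose one of two corrections to the drop-out sentence.

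- **Keep 299** and state that 81 and 218 allow for about 8.6% and 9.2% drop-out. This costs a sentence and no patients.
- **Keep the 10% allowance** and restate the targets as 83 + 220 = 303, or 84 + 222 = 306 if each arm is rounded up. This costs four or seven more patients.

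If the Stratum II base number is revised on other grounds, divide the new number by 0.90 instead of carrying 218 or 220 forward. In that case, settle the base number before adding patients to Stratum II on account of this point.

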### Statistical analysis

Differences between groups in continuous skewed main outcome variables will be analyzed by the Mann–Whitney U-test and t-test when variables are unskewed. Results are presented with 95% confidence intervals. Two-way-tables with the chi-square test will be used for dichotomous variables. Multivariate analysis will be conducted with regression analysis. In subgroup analysis the effect of age, sex, fracture group, smoking, and other diseases will be evaluated against the ROM, OSS, Constant-Murley, and overall quality of life after fracture.

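### Stratum II is sized on a three-group ANOVA, but the analysis section names only two-sample tests for the main outcomes. Three unadjusted pairs would carry about a 12% chance of a false-positive difference on DASH.

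*Protocol article*

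**What the plan says.** The Randomization section of the protocol article sets up three arms in Stratum II: "Patients with multi-fragmented fractures will be randomized to conservative, plate fixation, or prosthesis groups". The Methods/Design section gives the aim of that stratum as a comparison of all three treatments, and the Objectives section has the two strata reported separately.

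The Power analysis section sizes Stratum II with a three-group method: "the estimated sample size is 66 patients (ANOVA, alpha = 0.05, power = 0.8", followed by "The number of comparison groups is three" and "The total number of patients in Stratum II is 198".

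The Statistical analysis section then states the comparison of the continuous main outcomes for the whole trial: "Differences between groups in continuous skewed main outcome variables will be analyzed by the Mann–Whitney U-test and t-test when variables are unskewed". It adds 95% confidence intervals, chi-square tests for dichotomous variables, and regression for multivariate analysis with no model given. It mentions neither ANOVA nor Kruskal–Wallis, and it names no order of testing, primary contrast or adjustment. The Hypothesis section names DASH as the primary outcome and expects surgery to do better than conservative treatment.

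**The concern.** A t-test or a Mann–Whitney U-test compares two groups. The rule fits Stratum I, which has two arms. Stratum II has three arms, so the rule can be carried out only by testing pairs, whereas the sample size was derived for one overall test at 0.05.

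Two things follow. The declared 5% belongs to an overall test that the analysis section does not list, and pairwise tests each at 5% do not keep 5% for the stratum as a whole. In addition, the contrast that carries the conclusion is left open until the data have been seen. Stratum II holds 198 of the 272 patients counted before dropout, so this concerns the larger part of the trial.

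An ANOVA alone would not settle the hypothesis either, since it can be significant because plate and prosthesis differ from each other.

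**Working it through.** **Inputs.** All are from the Power analysis section: three groups, 66 per group, alpha 0.05, "assuming an effect size of a 10-point difference in the DASH score and a standard deviation of 15 points". Two-sided testing is not stated. It is an assumption supported by Stratum I: 37 per group is what a two-sided t-test needs, while a one-sided test would need about 29.

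**1. The plan's own figures.**
- Stratum I, "the estimated sample size is 37 patients (delta = 10, sd = 15, alpha = 0.05, power = 0.8": the exact two-sided t-test calculation gives 37 per group, so this reproduces.
- Stratum II: one-way ANOVA power comes from the noncentral F with 2 and 3(n − 1) degrees of freedom and λ = n·Σ(mean − grand mean)²/SD².
  - Means 0/5/10: Σ = 50 and λ = 50n/225. The smallest n with 80% power is 45 (power 0.806). At n = 66, λ = 14.67 and power is 0.936.
  - Means 0/0/10: Σ = 66.7. The smallest n is 34 (power 0.806). At n = 66, λ = 19.56 and power is 0.982.

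The figure of 66 therefore does not reproduce under either pattern of means; it is larger than needed. That is a separate matter. The error rates below hardly depend on n.

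**2. Three pairs, each at two-sided 5%, all arms equal.**
At least one pair is significant when the largest difference exceeds the t limit. With a pooled SD this probability is P(Q > √2 · t₀.₉₇₅,₁₉₅), where Q is the studentized range for k = 3 and 195 degrees of freedom. Since √2 × 1.972 = 2.789, P = 0.122. Simulation of pairwise t-tests (200,000 runs, 66 per arm) also gives 0.122. Simulation of Mann–Whitney tests on skewed data (20,000 runs) gives 0.117. For reference, three independent tests would give 1 − 0.95³ = 0.143, and the upper bound is 3 × 0.05 = 0.15.

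**3. Only the two surgery-versus-conservative pairs.**
The two contrasts share the conservative arm, so their correlation is 0.5.
- Either one significant in either direction: about 0.09 (simulated 0.090).
- Either one significant in favor of surgery: about 0.045. A single contrast gives 0.025, and the bound for two is 2 × 0.025 = 0.05.

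**4. With a three-group test as a gate.**
If pairs are tested only after an F-test significant at 0.05, the simulated chance of any false pairwise result with all arms equal is 0.050. If only one pair is truly equal, only one true null remains to be tested, at 0.05. So with three groups the two-step procedure keeps 5%.

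**5. Power per pair at 66 per arm.**
The noncentrality is 10/(15·√(2/66)) = 3.83.

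| Two-sided alpha per pair | Power |
|---|---|
| 0.05 | 96.7% |
| 0.025 | 94.0% |
| 0.0167 | 91.8% |

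**The case against.** The strongest reply is that the Statistical analysis section is one condensed paragraph for both strata. The two-sample tests may be meant for Stratum I, with the ANOVA in the Power analysis section implying the test for Stratum II. Details of error control are commonly left to a full protocol or analysis plan. This stands in part. Silence on an adjustment method would not be a finding by itself, and an ANOVA used as a gate would give 5%. But the article does more than stay silent: it states a rule for the main outcomes, does not restrict it to Stratum I, and that rule differs from the method used for sizing.

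It is also fair to say that the article never writes out three unadjusted tests with any one counting as success. The 12% is therefore conditional. The hypothesis, which sets surgery against conservative treatment, could be read as pointing to two contrasts, and then the figure is 9%.

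Two stronger readings are tempting. A reader might infer that the plan could falsely declare an operation better than conservative treatment at well above 5%. It could not: that probability is about 4.5%, because the 9% includes results in which surgery looks worse and the 12% also includes plate versus prosthesis. A reader might also infer that the mismatch leaves the stratum underpowered. It does not, under the stated difference and SD.

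**Conclusion.** The point holds as a contradiction within the protocol article: Stratum II is powered on a three-group ANOVA, while the stated analysis of the main outcomes uses two-sample tests and plain 95% intervals. Its size is about 12% for at least one false-positive difference on DASH across three pairs, and about 9% across the two surgery-versus-conservative pairs, against a declared 5%. In the direction that the hypothesis predicts, it is about 4.5% instead of the 2.5% of a single contrast.

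These figures assume two-sided tests at 5% without adjustment, 66 patients per arm and no true difference between arms. They do not show that an ANOVA will not be run; the analysis section does not exclude one, it only fails to list it. The wording should be settled before the Stratum II data are analyzed.

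**What to change.** In the Statistical analysis section, add a rule for Stratum II only, in one of two forms.

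- **Gate.** Test DASH across the three arms at 0.05, with an F-test if the scores are not skewed and Kruskal–Wallis if they are. Only if that test is significant, test the pairwise contrasts at 0.05 each, with t-tests or Mann–Whitney tests to match.
- **Named contrasts.** Make plate versus conservative and prosthesis versus conservative the two primary contrasts, with Holm control, or Dunnett where means are compared. Make plate versus prosthesis secondary. This form answers the stated hypothesis more directly.

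In either form, report each difference with its confidence interval. Keep the two-sample rule for Stratum I.

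The cost is wording and a slightly stricter requirement for each contrast. No patients need to be added under the stated assumptions: even at 0.0167 per pair, stricter than Holm on two contrasts requires, 66 per arm gives 91.8% power, and 80% would need 49 per arm. The F-test gate itself has 93.6% power with means 0/5/10 and 98.2% with 0/0/10.
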